### Determination of sample size and power calculation

The main objective is to evaluate the efficacy of a therapeutic protocol for the management of fatigue in schizophrenia patients. The change in fatigue level will be compared 6 months after the intervention (9-month follow-up) between two groups of patients: one following the 3-month individual program for the management of fatigue, and one receiving care as usual. The sample size calculation is based on the change in the general fatigue score, one of the five sub-scales of the Multidimensional Fatigue Inventory (MFI) [29], measured at inclusion and 9 months later.

A study exploring the psychometric properties of the MFI in 93 out-patients with schizophrenia spectrum disorders reported a mean score on the general fatigue subscale of 13.4 (standard deviation (SD): 3.9) [30]. An earlier study reported a mean score of 16 (SD 3.2) for this sub-scale in 166 patients with fibromyalgia and chronic widespread pain [49].

In our study of SZ patients attending a day hospital, with a general fatigue subscale score greater or equal to 10 at study entry, we can expect an average score of approximately 16 (SD 4) on this subscale.

We can also hypothesize a 2-point reduction in the mean score on this sub-scale between the start of the trial and the 9-month follow-up in the group receiving the intervention. No change in the severity of fatigue is expected in the group receiving treatment as usual. Under this effect-size hypothesis, with scores in both groups set at 16 (SD 4) at inclusion, the mean score in the group receiving the intervention is expected to drop to 14. Under the hypothesis of a stable standard deviation of 4 in both groups and at both time points, power set at .085 and alpha at *p* = 0.05, 73 patients per group are necessary.

In order to allow for loses at follow-up (estimated for SZ patients at 15–20% over a 9-month period), it will be necessary to recruit 100 subjects per group.

The 9 centers participating in this study are part of the French network of expert centers in schizophrenia of the FondaMental foundation. Participants will be recruited directly from the day hospitals in each of the centers.

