## Methods: assignment of interventions

### Randomization and matching

After checking for all inclusion and non-inclusion criteria by the study investigator, patients will be randomized to either of the study arms (intervention or TAU). Allocation concealment will be guaranteed as the randomization will not be released until the participant has been recruited into the trial, taking place after all baseline measurements have been done.

Randomization will be performed by the Clinical Research Unit of the Department of Medical Information of the Montpellier University Hospital. Randomization will be stratified by study center. It will be centralized, accessible online, and programmed using the data Capture Software System (EnnovClinical randomization module) according to a minimization algorithm with a 1:1 ratio. The trial manager will be responsible for setting up and testing the randomization process, incorporating stratification by study center using random blocks 1:1, assuring that study groups of approximately the same size will be produced.

The patient number will be automatically generated by EnnovClinical software.

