Another psychologist, from each center, will deliver the ENERGY therapy.

The physicians will be responsible in presenting the study (information, consent, inclusion) and following the patients during the entire study. Study nurses will be responsible in the management of blood sample, freezing, and shipment.

The methodologist will be in charge of the quality of the data and the statistics.

The laboratories implicated in the study will be in charge of the reception, storage, and analysis of blood samples.

GCP requires that the clinical protocol, any protocol amendments, the informed consent and all other forms of patient information related to the study (e.g., advertisements used to recruit patients), and any other necessary documents be reviewed by an Independent Ethics Committee (IEC)/Institutional Review Board (IRB). IEC/IRB approval of the protocol, informed consent and patient information, and/or advertising, as relevant, will be obtained prior to the authorization of enrolling patients in the study. The study shall be conducted as described in this approved protocol. Any revisions/amendments to the protocol will not be permitted without prior approval by the study steering committee. Any amendments to the protocol will require IEC/IRB approval prior to implementation of any changes made to the study design.

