#### Main endpoint analysis

The efficacy of the ENERGY intervention will be studied firstly by comparing the change in fatigue score (using the scores on the MFI) between inclusion/randomization and the 9-month follow-up (primary outcome) in the intervention group compared to the TAU group.

For each subject, the relative difference (delta) between the inclusion and 9-month fatigue score will be calculated. The normality of the delta score will be tested using the Shapiro Wilk’s test. If the distribution is skewed a transformation will be performed to normalize it.

Study arms will be compared between inclusion scores and the 9-month scores using mean differences. These comparisons will be done using Student’s *T* test and general linear regression models adjusting for covariates. Socio-demographic and clinical variables will be tested as potential confounders using general linear regression models, with the *p* value set at 0.10.

A second analysis will be carried out with the general fatigue score as the outcome variable, adjusting for general fatigue score at inclusion.

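### The primary comparison has no named deciding analysis: an unadjusted t test sits beside linear models whose covariates are picked by a p = 0.10 test, and centre, the stratification factor, is not named

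*Protocol article*

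**What the plan says.** **Analysis.** Under Main endpoint analysis, the change in MFI score from inclusion to 9 months is compared between arms by Student's t test and by general linear models with covariates. On the choice of covariates the text says: "Socio-demographic and clinical variables will be tested as potential confounders using general linear regression models", with the threshold at 0.10. The candidates are not listed, and it is not said whether they are tested against the outcome or against arm. A second analysis takes the general fatigue score as outcome and adjusts for its baseline value. No rule says which of these results is the primary one. Neither centre nor therapist appears anywhere in the Statistical analysis section.

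**Allocation.** Under Randomization and matching: "Randomization will be stratified by study center". The same paragraph describes the allocation as working "according to a minimization algorithm with a 1:1 ratio" and then as "incorporating stratification by study center using random blocks 1:1".

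**Delivery.** Under Trial governance and monitoring: "Another psychologist, from each center, will deliver the ENERGY therapy". Sessions are individual.

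**The concern.** In a randomised trial, baseline differences between arms arise by chance, so significance tests are a poor way to choose adjustment variables. A screen over an open list means that nobody can write down the adjusted primary model before the data are seen. With an unadjusted test alongside it and no rule between them, two or more primary p values will exist and any of them could be presented as the result. The strongest covariate one would expect, baseline fatigue, is guaranteed a place only in the second analysis. The factor that shaped the allocation, centre, is guaranteed a place in none.

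What is at stake is whether the primary result is fixed in advance and, to a lesser degree, whether its standard error reflects the stratified design.

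**Working it through.** **1. The plan's own sample size.** The inputs are "a 2-point reduction in the mean score on this sub-scale between the start of the trial and the 9-month follow-up" with no change under usual care, and "Under the hypothesis of a stable standard deviation of 4 in both groups and at both time points". The text gives "power set at .085 and alpha at *p* = 0.05, 73 patients per group are necessary". With difference 2, SD 4 and two-sided alpha 0.05, a power of 0.85 gives n = 2(1.960 + 1.036)² × 4²/2² = 72 per group by the normal formula and 73 by the t distribution. The printed power is therefore a misprint for 0.85. The calculation treats patients as independent, with no centre or therapist term. A 20% loss from 100 per group leaves 80 per arm, the size used below.

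**2. How many candidates?** The article records 7 socio-demographic items, 4 medical-history items and 10 baseline scales for symptoms, sleep, activity, quality of life, functioning and motivation: 7 + 4 + 10 = 21 before subscales. A range of 10 to 30 is assumed. The chance that at least one pure-noise candidate passes p < 0.10 is 1 − 0.9^K, which is 65%, 88% and 96% for K = 10, 20 and 30 (independent candidates).

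**3. Type I error.** Simulation under no effect, 80 per arm, 6,000 runs per row (Monte Carlo standard error √(0.05 × 0.95/6000) = 0.003). R² is the assumed share of outcome variance explained by covariates.

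| K | R² | t test | Screened on outcome | Screened on arm | t test or outcome-screened |
|---|---|---|---|---|---|
| 10 | 0 | 0.0490 | 0.0498 | 0.0505 | 0.0548 |
| 20 | 0 | 0.0470 | 0.0492 | 0.0470 | 0.0577 |
| 30 | 0 | 0.0495 | 0.0507 | 0.0488 | 0.0600 |
| 10 | 0.20 | 0.0497 | 0.0500 | 0.0427 | 0.0715 |
| 20 | 0.20 | 0.0535 | 0.0515 | 0.0432 | 0.0753 |
| 30 | 0.20 | 0.0512 | 0.0503 | 0.0447 | 0.0718 |

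If the arm-screened model may be claimed as well, the maximum is 0.081. A second simulation, taking R² up to 0.40, gave 0.046–0.054 for the screened model alone. For the either-result rule it gave 0.056–0.059 with noise covariates and 0.069–0.083 with R² of 0.20 to 0.40.

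**4. Leaving out centre.** If centre carries a share ρ of outcome variance and allocation is balanced within centre, the unadjusted standard error is too large by 1/√(1 − ρ). For ρ = 0.01, 0.05 and 0.10 the factor is 1.005, 1.026 and 1.054, and the real alpha is 0.049, 0.044 and 0.039.

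**5. Therapist, if there is one per centre.** The Participants section gives eight centres of 20 and one of 40. With 80 ENERGY completers that is eight clusters of 8 and one of 16, with weighted size (8 × 8² + 16²)/80 = 9.6. The ENERGY-arm design effect is 1 + 8.6 × ICC, and the standard error ratio is √((1 + design effect)/2).

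| ICC (assumed) | Design effect | True SE / naive SE | Real alpha | Power with correct SE |
|---|---|---|---|---|
| 0.01 | 1.09 | 1.02 | 0.055 | 0.87 |
| 0.02 | 1.17 | 1.04 | 0.060 | 0.86 |
| 0.05 | 1.43 | 1.10 | 0.075 | 0.82 |
| 0.10 | 1.86 | 1.20 | 0.101 | 0.75 |

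Power without clustering is 0.885.

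**The case against.** The best defence is that this is a condensed article and that the SAP is due before database lock. The word covariates is open, so centre could still be included; the document is silent on it and does not exclude it. That stands, and it makes the centre and therapist parts weaker than the rest. It does not rescue the screen, the unranked pair of analyses or the two allocation methods, because the article states these itself. Blinding the analysts to group does not help either: a two-sided p value is the same under masked labels.

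Three stronger readings are tempting and are not supported.

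- **The screen inflates type I error.** Section 3 of the working shows that, used alone, it does not.
- **The trial will run at 7 to 8% type I error.** That needs a rule under which either result may count, which the article never states, and covariates explaining 20 to 40% of variance, which it does not give.
- **The t test is invalid because one therapist treats every ENERGY patient at a centre.** The governance wording suggests this but mainly separates therapist from assessor and fixes no number. The article says all teams are trained, and the therapy is individual and follows a manual, which gives no reason to expect a high ICC. More therapists per centre would mean smaller clusters and smaller design effects. The ICC is unknown.

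Omitting centre is also conservative: it costs a little precision and does not raise the error rate.

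**Conclusion.** The point holds in a limited form. The primary comparison is not fixed to one analysis, and its adjusted version depends on a data-driven choice among unlisted variables. The screen by itself keeps type I error at about 5%. The exposure lies in the freedom to choose between results: about 5.5 to 6% if the covariates are noise and about 7 to 8% if they explain 20 to 40% of variance, both under an either-result rule that is an assumption. Leaving out centre makes the standard error roughly 0.5 to 5% too large for an assumed centre share of 1 to 10%. A therapist effect would act in the opposite direction, but its size rests on an assumed ICC and an inferred head count, so it supports a sensitivity analysis and no more.

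The two allocation methods are a separate contradiction. Minimisation and centre-stratified random blocks are different procedures, and the article attributes both to the same trial.

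**What to change.** 1. Delete the p = 0.10 screen, or keep it only as a labelled sensitivity analysis.
2. Name one decisive primary model: 9-month score on arm, the baseline value of the same score, and centre. The score must be whichever MFI score is declared primary. The article uses the MFI score in the outcome section and the general fatigue subscale in the sample size, and this fix does not choose between them. The t test becomes supportive.
3. As a sensitivity analysis only, add a random therapist effect in the ENERGY arm, with small-sample degrees of freedom. A centre-by-arm effect does the same job only if there is one therapist per centre. A fixed centre term alone would not capture it, because the therapist acts in one arm.
4. Under Randomization and matching, keep the algorithm actually programmed and delete the other.

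The cost is wording in the protocol and SAP. Nine centres use up to 8 degrees of freedom: with 160 completers, the residual falls from 160 − 2 = 158 for the t test to 160 − 1 − 1 − 1 − 8 = 149, which is negligible. Keeping the therapist term out of the primary model avoids tying the main result to an ICC that nobody has yet estimated. If clustering is real, the sensitivity interval will be wider, by about 10 to 20% at an ICC of 0.05 to 0.10.

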#### Secondary endpoint analysis

The secondary outcome analyses will be assessed similarly to the main endpoint analyses. Specifically, for normally distributed variables, means and standard deviations will be used to conduct the analyses, whereas for skewed variables, medians and ranges will be used.
A secondary outcome variable will be constructed, measuring the change in fatigue score (based on MFI scores) between inclusion scores and the 3-month follow-up, representing the end of the ENERGY intervention (for the intervention study arm). Change in fatigue score over the three time points using mean differences in scores between the intervention and TAU study arms will be compared using a mixed-effects model, taking into account the repeated and reversible time-dependent outcome measures.Assessment of the effect of the intervention on a range of exploratory outcomes (clinical and cognitive factors, biological markers) measured at the 9-month follow-up will be carried out using either linear regression models or logistic regression models, depending on the type of variable (continuous or binary). These scores will be compared to the initial scores obtained at inclusion. For each outcome variable, the model will be adjusted for the baseline value. These secondary analyses will include measures of:
◦ General symptomatology—scores of the PANSS◦ Severity in negative symptoms—scores of the CAINS◦ Depression—scores of the CDSS◦ Risk of sleep apnea—scores on BQ◦ Hypersomnolence—scores on IHSS◦ Insomnia—scores on SCI◦ Level of physical activity—scores on IPAQ◦ Quality of life—scores on S-QoL◦ Functional remission—scores on FROGS◦ Level of intrinsic motivation—scores on IMI-SR◦ Intellectual ability—scores on fNART◦ Learning and recall—scores on CVLT◦ Attention—scores on TMT◦ Weight, BMI, abdominal perimeter, hearth rate, blood pressure◦ Number of steps and distance covered over a week using the pedometerA sub-group analysis will be performed on the intervention arm of the RCT, to identify potential factors that are linked to efficacy of the intervention. This main outcome variable will be the change in fatigue score between inclusion and the 9-month follow-up. Linear regression models will be constructed to study the effect of each dependent variable, individually and altogether in a multi-adjusted model, on the outcome.Additionally, a cross-sectional analysis of baseline data will be performed to study the biological (inflammatory markers, microbiota) and psychological factors associated with fatigue severity, overall and on each of the five MFI sub-scales, using general linear regression models.

Modifications to the initial SAP will require an amendment to the protocol. Exploratory statistical analyses not documented in the initial SAP will be discussed by the co-investigators and statisticians, in order to establish their importance and acceptability with respect to the study’s main and secondary objectives.

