#### Primary outcome measures

The primary outcome measure is the score at the Multidimensional Fatigue Inventory (MFI) [29]. The MFI is a self-assessment instrument with 20 items including 5 dimensions: General, Physical, and Mental Fatigue; Reduced Motivation; and Reduced Activity. It was validated in 93 patients with schizophrenia spectrum disorders. The test–retest showed a correlation between .66 and .91 for all subscales of MFI. The internal consistency was .92. The analysis of convergent construct validity showed a correlation of .68 (time 1) and .77 (time 2). No item was systematically identified as being difficult to answer [30].

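### Factors said to be linked to efficacy are sought in the intervention arm alone, so prognosis and regression to the mean are likely to be reported as differential benefit

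*Protocol article*

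**What the plan says.** All of the following is in the Protocol article.

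- **Population and aim** (Secondary endpoint analysis): a "sub-group analysis will be performed on the intervention arm of the RCT, to identify potential factors that are linked to efficacy" of the intervention.
- **Outcome** (same section): "This main outcome variable will be the change in fatigue score between inclusion and the 9-month follow-up".
- **Model** (same section): "Linear regression models will be constructed to study the effect of each dependent variable, individually and altogether in a multi-adjusted model, on the outcome". From the context, the variables called dependent here are the explanatory factors. They are not listed.
- **Baseline adjustment** (same section): for the exploratory outcomes compared between arms, "For each outcome variable, the model will be adjusted for the baseline value". This is not repeated for the intervention-arm analysis.
- **Meaning of efficacy** (Main endpoint analysis): change in fatigue in the intervention group set against change in the TAU group.

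The Statistical analysis section and its subsections state no factor-by-arm interaction and no other search for effect modifiers that uses TAU. TAU patients are assessed at the same three visits.

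**The concern.** Efficacy in this protocol is a contrast between arms. Change within the treated arm has at least three components: the effect of therapy, the course the patient would have had anyway, and regression to the mean after selection on a fatigue score. A regression of that change on a factor, fitted in one arm, picks up an association with any of the three and cannot say which. The TAU arm shows the second and third without the first, but this analysis does not use it.

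At stake is the interpretation of a secondary result. A factor that marks patients whose fatigue changes regardless of therapy could be published as a factor linked to the therapy's efficacy.

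**Working it through.** **Plan's own figures.** The plan gives no figure for this analysis. Its sample size can be checked because the inputs are reused below. With a difference of 2, SD 4, two-sided alpha 0.05 and power 85%, n = 2 × (1.960 + 1.036)² × 4² / 2² = 71.8, so 72 per group by normal approximation against 73 stated. (Power is printed as .085; 0.85 reproduces the figure.) Recruiting 100 per group and losing 20% leaves 80.

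**Inputs**

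- Baseline general fatigue: "we can expect an average score of approximately 16 (SD 4) on this subscale"; the same SD is assumed at both times (Determination of sample size and power calculation).
- Entry cut: "with a general fatigue subscale score greater or equal to 10 at study entry" (same section).
- Effect: "We can also hypothesize a 2-point reduction in the mean score on this sub-scale" under intervention, none under TAU (same section). Here it is applied equally to every patient, so true effect modification is zero.
- Test-retest: "correlation between .66 and .91 for all subscales of MFI" (Primary outcome measures). The 9-month correlation r is not given; using this range for it is an assumption.
- 80 completers in the intervention arm.

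**Route 1: regression to the mean, with baseline fatigue as the factor, no entry cut.** With equal SDs, corr(baseline, change) = −√((1 − r)/2). The chance of p < 0.05 follows from Fisher's z: Φ(atanh|corr| × √77 − 1.96), plus a negligible opposite tail.

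**With the entry cut.** Truncating a normal (16, SD 4) at 10 reduces the baseline SD to 3.52. The slope of change on baseline is −(1 − r) and the residual SD is 4√(1 − r²), so

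corr = −(1 − r) × 3.52 / √[((1 − r) × 3.52)² + 16(1 − r²)].

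At r = .66 this is −1.195 / √(1.429 + 9.030) = −0.370; then atanh(0.370) × 8.775 − 1.96 = 1.44, and Φ(1.44) = 0.93.

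| r | corr, no cut | flagged | corr, with cut | flagged |
|---|---|---|---|---|
| .66 | −0.41 | 97% | −0.37 | 93% |
| .80 | −0.32 | 82% | −0.28 | 72% |
| .91 | −0.21 | 47% | −0.19 | 38% |

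A simulation of 4,000 trials per case agrees: 97%, 83% and 48% without the cut; 92%, 72% and 37% with it. The arm-by-baseline interaction test, using 80 per arm, flagged about 5% in every case.

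**Factors merely correlated with baseline fatigue.** At r = .66 without the cut, and assumed correlations of 0.3 and 0.5 with baseline, simulated within-arm flag rates are 20% and 46%. Adjusting for baseline fatigue brings both back to 5%.

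**Route 2: prognosis.** Take a factor independent of baseline fatigue that shifts the 9-month score equally in both arms (r = .66, no cut; sizes are assumptions). For 1 point per SD, the SD of change is √(2 × 16 × 0.34) = 3.30, so corr = 1/3.30 = 0.30 and the flag rate is 78%. Simulated rates:

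| Points per SD | Within arm | Within arm, baseline-adjusted | Interaction, both arms |
|---|---|---|---|
| 0 | 5% | 5% | 5% |
| 0.5 | 28% | 32% | 5% |
| 1.0 | 78% | 86% | 5% |
| 1.5 | 99% | nearly 100% | 5% |

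Baseline adjustment closes the first route but not the second.

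**Price of the interaction test.** With 80 per arm, the interaction detectable at 80% power is 2.80 × 4√(1 − r²) × √(2/80): 1.3 points per SD of factor at r = .66 and 1.1 at r = .80, against an assumed overall effect of 2 points.

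**The case against.** The analysis is secondary, it speaks only of potential factors, and none of the stated objectives or hypotheses depends on it. A predictor of change under therapy is a genuine association; it misleads only when read as differential benefit. The largest figures concern baseline fatigue, which the plan does not name as a factor, and a multi-adjusted model could include it. The suggested replacement has little power.

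Much of this stands. It limits the weight of the point and supports relabelling as an acceptable remedy. It does not remove the problem: the stated aim is efficacy, the single-factor models carry no stated baseline adjustment, and adjustment leaves prognosis untouched. Population, outcome and model are all fixed in the text, so this is not a detail left open for the SAP. Low power is a reason to report wide intervals, not to use a test that answers a different question.

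A reader might infer that the analysis is certain to produce false effect modifiers. The documents do not support that: a factor unrelated to both baseline fatigue and prognosis is flagged at the nominal 5%, and the candidate factors are not listed. Nor do they propose using the results to select patients for therapy, and TAU is left out of this analysis only, not of the efficacy comparisons.

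**Conclusion.** The point holds as a likely misattribution, not a certain one. The planned within-arm regression cannot separate differential benefit from prognosis or regression to the mean, so factors it flags should not be described as linked to efficacy. If baseline fatigue is among the factors, it would be flagged in about 93% to 38% of trials with the entry cut and 97% to 47% without it, although therapy works identically for everyone.

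These figures rest on normal scores, 80 completers, the cut applied to the general fatigue subscale, and a 9-month correlation within the test-retest range. The prognostic effect sizes are illustrative. The primary result and the between-arm secondary comparisons do not change. The text should be corrected, with priority below anything that touches the primary analysis.

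**What to change.** Use both arms. Model the 9-month value of whichever fatigue score serves as the primary outcome on arm, baseline fatigue, factor and arm-by-factor interaction. Do this for a short list of factors named in advance, and report the interaction estimates with 95% confidence intervals as exploratory. When baseline fatigue is itself the factor, the interaction is arm by baseline fatigue.

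If the intervention-arm model is kept, describe it as predictors of change under therapy (prognostic), not of efficacy.

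No new data or patients are needed. The sentence stands in the protocol, so the change is a protocol text amendment; under Trial governance and monitoring, amendments need steering committee and ethics approval. The interaction intervals will be wide.
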